Description of the Active Brains intervention using the Template for Intervention Description and Replication checklist.1. Brief nameActive Brains Study2. WhyAn aging population places strains on health services: particularly with the increase in dementia. Several lifestyle changes have been found to help protect against cognitive decline. The aim of this study is to develop and test a digital behavior change intervention to help older adults increase their physical activity, improve their diet and practice cognitive 'Brain Training' activities to reduce cognitive decline.3. What material?Assessment: All participants will complete web-based questionnaires and complete the four cognitive assessment games at 0 and 12 monthsIntervention Group: Participants in this group receive access to the Active Brains digital intervention.Intervention with support group: Participants in this group will receive the Active Brains digital intervention and additionally will be offered up to eight 10 minute support phone calls with a trained supporter.Control Group: Participants in this group will receive usual care from their GP and brief web-based advice about getting more active, improving diet and staying mentally active.The Active Brains Digital Intervention contains 4 sections described below.Month 0: Active Brains Starter Section. Access to 'Active Lives', including 'Strength and Balance', 'Taking Breaks from Sitting' and 'Getting Active'. These modules contain: Information addressing common concerns; Provision to order a step counter and guidance on using it; User stories modeling overcoming barriers; Instructions about obtaining social support; Suggestions for environment restructuring; Instructions about recommended activities (including Strength and Balance videos); Facilities to set, plan and review goals about their chosen activities; Tailored motivational feedback about their progress; Reminder emails to motivate them to continue with their activities and to revisit intervention content as appropriate.Month 1: Access to Brain Training. This module provides: Brief information about the rationale and evidence base for Brain Training tasks and how they are intended to work; User stories modeling overcoming barriers; Access to six web-based brain training games (via the existing PROTECT website) which they are encouraged to play between three and five times per week; facilities to set, plan and review goals about their chosen activities; tailored motivational feedback about their progress; reminder emails to motivate them to continue with their activities; Six additional games are made available to users during months 1-6Month 2: Access to Eat for Health. This module contains: Information on the benefits of healthy eating for cognitive and physical health; Information and techniques to allow them to make healthy changes to their existing eating behaviors (eg, increasing fruit and vegetable consumption, cutting down on processed foods); Facilities to set, plan and review goals about their chosen activities; User stories modeling overcoming barriers; Tailored motivational feedback about their progress; Reminder emails to motivate them to continue with their activities; RecipesMonth 6: Transition to Active Brains Booster Section. This module contains: Tailored summary of their progress and engagement with the Starter Section content; Links to additional resources for additional support and to extend their progress with the behavioral changes made.The content was developed to support self-efficacy and autonomy. It used simple and accessible language, using persuasive rather than directive phrasing (ie, “you can” rather than “do”), and promoting guided choice rather than direction (eg, offering a range of ideas for goals).4. What procedureScreening and randomization: Participants will complete web-based screening to ensure eligibility. Participants will then complete cognitive tasks and the Instrumental activities of daily living (IADL) questionnaire to determine work stream (with or without cognitive impairment). If the assigned work stream is full (capped at n=180), participants will be given access to Active Brains (no support) as part of a cohort study. Participants in each work stream will be randomized to one of the three groups. They will be informed of their group allocation on the website immediately.Intervention Group: Participants will receive full access to the Active Brains intervention. They will receive regular emails to remind them to access the intervention. They will be sent reminder emails when follow-up measures are available to complete.Intervention with Support Group: Participants will receive full access to the Active Brains intervention. Participants in this group will additionally be sent emails from an assigned supporter. They will be invited to book phone call appointments to support them with their use of the intervention.Control Group: Participants will receive basic information online about getting more active, improving diet and staying mentally active. They will be sent reminder emails when follow-up measures are available to complete.5. Who providedAssessment: Participants will be invited to take part using a letter from their GP practice. They will access the screening and measures online.Intervention Group: Participants will use the intervention online.Intervention with Support group: Participants will additionally be provided with support from trained supported from the university of Southampton. These are members of the research team who have completed brief web-based training in the CARE approach. The CARE (Congratulate, Ask, Reassure, Encourage) approach is intended provide support to patients based on Self-Determination Theory. Supporters will also offer technical support.6. HowIntervention delivered entirely online.Follow-up procedures may include telephone and post.7. WhereIntervention delivered entirely online, intended to be used in the participant's home.8. When and how muchIntervention Group: The intervention is divided into a 'Starter Section', lasting 6 months and a 'Booster' section provided at 6 months. The starter section unlocks 'Active Lives' at month 0, 'Brain Training' at month 1 and 'Eat for Health' at month 2. Participants will be encouraged to set goals and plans for each section and return to review the goals after one week. After 'Brain Training' unlocks, participants will be encouraged to set a goal to play the games 3-5 times a week until month 6, and then play for 3-5 times a week for a month every 3 months. Initially 6 games will be available with new games unlocking every month until 12 games are available. Participants will be guided to form healthy habits so that after 6 months they will be less reliant on the intervention. For participants with a BMI>30, a weight loss tool 'POWER' will be offered at month 6.Intervention with support group: In addition to the intervention, these participants will be offered three support phone calls at weeks 2, 6 and 10. They may request up to 8 phone calls in total.9. TailoringThe intervention will tailor physical activity recommendations to self-rated Strength and Balance and current physical activity. Participants may then choose any or all of the three physical activity modules.Strength and balance exercises are tailored to self-rated strength and balance.The weight loss tool will only be offered to participants with a BMI>30.Goal review feedback will be tailored to prior performance (the past two review ratings for that module).10. ModificationThe intervention will not be modified during the trial.11. How wellThe intervention was created using the Person-Based Approach (PBA). Experts in digital behavior change oversaw the development. End users were consulted at all points of development and the intervention was iteratively refined to overcome anticipated barriers. The intervention was thoroughly tested by the research team to ensure that there were minimal problems with the software.

Participants will be encouraged to set and review goals every week when using Active Brains. When they unlock “Brain Training,” they will be encouraged to play the games 3 to 5 times per week for the first 6 months. The intervention will be available to the participants for a year. However, the Active Brains intervention aims to help participants establish healthy habits (eg, regular walking) so that participants are not dependent on the intervention in the long term—we anticipate that participants will not need to use the website every week for 6 months to gain benefits from the intervention. The level of engagement that is effective in improving outcomes will be investigated in the main trial.

### Central Facilitator Support

Patients in the group receiving support from a central facilitator (in addition to the website) will be offered a brief (10 min) telephone support call 2 weeks after they begin the study. In this support call, they will discuss the cognitive or lifestyle changes that they are planning to try. Patients will be offered 2 more support contacts by phone (up to 10 min) or email to support them in making behavioral changes.

Central facilitators will be people trained in the congratulate, ask, reassure, and encourage (CARE) approach to provide support to patients, which is based on Self-Determination Theory [72] and designed to promote autonomous motivation for making behavioral changes. This approach has been successful in previous trials [73].

### Usual Care

The comparison group will receive usual care from their GP practice, in addition to brief web-based advice about becoming more physically active, improving the diet, and staying mentally active.

### Outcome Measures

Table 1 presents a list of the measures and when they will be presented to participants. Participants will receive follow-up reminders by email, post, and telephone and by contacting a nominated contact person (optional). If no contact is successful, the contact person will be asked to help put the research team in touch with the participant or to complete 3 short questionnaires about the participant (EQ-5D-5L proxy version 2 [55], IADL [49], and Informant Questionnaire on Cognitive Decline in the Elderly [70]).

### Participant Timeline

Participants will register, be randomized, and complete baseline measures. Participants in the intervention arm will then be given access to the intervention, which they can use for one year. Participants in the support arms will be invited to have a support call at weeks 2, 6, and 10. A sample of participants will be invited to participate in a qualitative process interview at 6 months. All participants will be invited to complete outcome measures at 12 months.

### Sample Size

This is a feasibility trial, so it was not powered to measure patient outcomes. A sample size of 180 for each of the 2 subgroups was chosen for several reasons. As Active Brains is a digital intervention with multiple possible pathways through it, a sufficiently large group would be required to observe different patterns of usage. Fully web-based interventions are easy to recruit and manage larger numbers of participants, making this possible. The proposed fully powered trial would need to recruit over 20,000 patients, so implementation issues and trial processes (eg, managing multiple supporters) needed to be tested at scale. A total of 360 participants would provide robust evidence for the feasibility of the trial.

### Data Collection, Management, and Analysis

Outcome measures will be collected by using the software at registration and at one year. It will be held securely in a database accessible only by the data controller and members of the study team. Each participant will be assigned a unique study ID when they register with the website. Anonymous outcome data will be held in a separate write-only database to the personally identifiable data to ensure blinding and guard against modification.

Personally identifiable data will be held in accordance with the General Data Protection Regulation [74]. It will only be accessible to members of the study team throughout the study to monitor usage and provide support. The data will be analyzed by a statistician who has had no access to these data.

#### Statistical Analysis

The primary analysis will determine whether the feasibility trial has met the stop or go criteria and will therefore describe the completeness of the data in relation to the number of participants recruited.

Data for the secondary analyses will be explored descriptively and graphically for the other key feasibility outcomes, including intervention uptake, adherence, attrition, retention, and the number of participants recruited per practice. We will estimate the variability of proposed outcome measures and discuss any implications for the sample size for the full trial.

All participant data will be analyzed, including those who have withdrawn, unless the participant specifically requests for their data to be removed. All participants will be analyzed as randomized. The pattern and frequency of missing data will be explored descriptively in the feasibility context to determine whether there are whole instruments or items on instruments that participants opted not to complete and to inform the stop or go decision for the full trial.

The same outcomes will be assessed in a cohort study to explore whether it is feasible to recruit additional participants and collect data to inform future implementation in this way.

For the feasibility study, we will provide only descriptive estimates (ie, we will not be performing an inferential analysis to establish whether there are significant differences between groups).

#### Health Economic Analysis

At this feasibility stage, we aim to collect resource usage information associated with the intervention and explore and identify the likely changes in practice due to the intervention through questionnaires, case note review, and qualitative interviews. We plan to develop and refine the methods for collecting such information and to inform the choice of which instrument will be used to measure quality of life for the later planned, fully powered trial.

The study will explore both the National Health Service (NHS) and social service perspectives. All itemized resource usage will be costed using published information (eg, the Personal Social Services Research unit [75], the BNF [76]). Quality of life will be measured using EQ-5D [55], ICECAP [56], and SF-12 [57] at baseline and 12 months. We will apply the UK tariff to translate the questionnaire scores to utility scores. We aim to test the sensitivity and feasibility of these instruments in the study population, hence informing the choice of the instrument in the full trial.

The economic analyses of costs and quality of life will be mainly descriptive (with mean and standard deviation). We will correlate all utility scores with the planned primary outcome [50] to see the magnitude of sensitivities. The focus will be on the direction of correlation, spread, and confidence intervals.

Such information will allow us to investigate the most relevant resource use of information to be collected and inform choice of the quality of life instrument to be used in the definitive trial.

### Qualitative Process Analysis

There will be 2 qualitative process studies, one with participants and one with central support facilitators. Interviews in both these studies may be carried out at any time between 2 and 12 months after participants begin the study. Both of these studies will allow assessment of the acceptability and feasibility of the intervention and highlight any modifications to the intervention or study procedures that might be required before embarking on the later planned, fully powered trial.

#### Qualitative Process Study With Participants

We will interview 12 to 18 participants from each of the intervention arms, employing purposive sampling to ensure a diverse range of participants in terms of demographic and clinical profiles as well as website usage. Participants will be invited to participate by the research team and asked if they would be willing to take part in a telephone interview. They will complete a separate consent form (online) before taking part in an interview. During the interview, open-ended questions will be used to explore participants’ perceptions of the study, the website (if in one of the intervention groups), and the support they received from the central facilitator (if in the support group). Those in the control group will be asked about the brief advice they were given at baseline.

#### Qualitative Process Study With Central Support Facilitators

The second substudy will use face-to-face or telephone interviews to explore central support facilitators’ views of the study procedures, the website, the training they were provided, and the support they provided to patients (including perceptions of the CARE approach).

#### Analysis

Data from both qualitative process studies will be analyzed using inductive thematic analysis with interrater agreement reached between team members. The findings will be discussed and interpretations agreed between the coinvestigators (including PPI representatives).

### Monitoring Adverse Events

Serious adverse events (SAEs) will be reported by both participants, practice staff, and possibly by the central support facilitators who will have contact with participants during the study. It is not anticipated that SAEs will be related to this research. SAEs are defined as any untoward medical occurrence or effect that at any dose results in death, is life threatening, requires hospitalization or prolongation of existing hospitalization (excluding hospitalization for pre-existing conditions or planned procedures), results in persistent or significant disability or incapacity, is a congenital anomaly or birth defect, or results in other important medical events. Any SAE occurring to a research participant will be reported to the ethics committee where, based on the initial judgement made by the chief investigator or an agreed deputy, the event was related to the administration of any of the research procedures and was an unexpected occurrence. Nonserious adverse events will not be collected.

GP practices and the central support facilitation staff will inform the research team and/or the Clinical Trials Unit of any SAEs within 24 hours of them being aware of the event occurring. GP practices and central support facilitation staff will be provided with a standard operating procedure and a form for SAE reporting. Patients may also report SAEs. Reports of SAEs will be provided to the ethics committee within 15 days of the chief investigator becoming aware of the event. In addition to the chief investigator making the initial judgement about the SAE, all SAEs will also be sent to the trial steering committee for adjudication.

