**Exclusion criteria**
High levels of leisure time physical activity (score ≥30 on Godin Leisure Time Exercise Questionnaire [47] (moderate or vigorous physical activity only)Another member of the household already participating in the study

**Table 1 table1:** Outcome measures and times presented to each group for the Active Brains feasibility trial.

Measure		Time		Group			
		Baseline	12-month follow-up	Usual care	Active Brains intervention	Active Brains intervention and support from central facilitator	Nonrandomized cohort study participants (receiving the Active Brains intervention)
Sociodemographic data		✓^a^	—^b^	✓	✓	✓	✓
Clinical and behavioral data		✓	✓	✓	✓	✓	✓
Clinical measures (from notes review)		—	✓	✓	✓	✓	—
Cognitive Performance Tasks [50-53]		✓	✓	✓	✓	✓	✓
Instrumental Activities of Daily Living [49]		✓	✓	✓	✓	✓	✓
The Patient Enablement Scale [48]		—	✓	✓	✓	✓	✓
International Physical Activity Questionnaire [54] plus strength and balance items^c^		✓	✓	✓	✓	✓	✓
EQ-5D-5L^d^ [55]		✓	✓	✓	✓	✓	✓
EQ-5D-5L-proxy version 2 (for contact person completion if required) [55]		—	✓	✓	✓	✓	—
ICEpop CAPability measure [56]		✓	✓	✓	✓	✓	✓
Short-form Health Survey [57]		✓	✓	✓	✓	✓	✓
Dementia diagnosis (from notes review)		—	✓	✓	✓	✓	✓
Mortality		—	✓	✓	✓	✓	—
Health economic analysis of cost-effectiveness (from notes review)		—	✓	✓	✓	✓	—
Food Frequency Questionnaire [58]		✓	✓	✓	✓	✓	✓
Problematic Experiences of Therapy Scale [59]		—	✓	—	✓	✓	✓
Brief Geriatric Depression Scale [60,61]		✓	✓	✓	✓	✓	✓
Self-efficacy for exercise [62]		✓	✓	✓	✓	✓	✓
Medical Outcome social support Survey [63,64]		✓	—	✓	✓	✓	✓
Social Support for Exercise [65]		—	✓	✓	✓	✓	✓
Locus of Causation in Exercise [66]		✓	✓	✓	✓	✓	✓
Technology Acceptance Model Perceived Ease of Use scale [67-69]		—	✓	—	✓	✓	✓
Informant Questionnaire on Cognitive Decline in the Elderly–short form (if participants do not complete full measures) [70]		—	✓	—	✓	✓	—

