### Assignment of Interventions

Simple randomization will be used to assign participants to intervention arms using the study software’s computer-generated random numbers. Randomization occurs online after a participant completes baseline measures, ensuring blind randomization. They will have an equal chance of being in each of the 3 groups. Once randomized, participants will be informed of their group allocation (they will also be emailed this information). If participants are in one of the treatment arms, they will be taken directly to the Active Brains intervention. These participants can then use the Active Brains intervention as much as they would like to over the course of the study. The central facilitator will be notified by email when a participant is randomized to the support arm of the trial, so that they know to expect to provide support to the participant in the coming weeks. Research staff will not be blinded to the participant group but the statistician and health economists conducting the analyses will be.

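### Facilitators are an extra possible SAE reporter in the support arm only, so that arm's SAE count is expected to be equal or higher at the same true risk

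*Protocol article*

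**What the plan says.** Monitoring Adverse Events names three routes by which an SAE can reach the team: participants, practice staff, and "possibly by the central support facilitators who will have contact with participants during the study". The professional routes carry a duty: "GP practices and the central support facilitation staff will inform the research team and/or the Clinical Trials Unit of any SAEs within 24 hours" of becoming aware of the event. Both practices and facilitators receive a procedure and a form. The participant route is voluntary: "Patients may also report SAEs". All reported SAEs go to the trial steering committee for adjudication. Nonserious events are not collected.

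Facilitator contact is described for one arm. Assignment of Interventions says "The central facilitator will be notified by email when a participant is randomized to the support arm of the trial". Central Facilitator Support says "Patients in the group receiving support from a central facilitator (in addition to the website) will be offered a brief (10 min) telephone support call" at two weeks, with two further contacts by phone or email. Participant Timeline gives the schedule: "Participants in the support arms will be invited to have a support call at weeks 2, 6, and 10". The TIDieR textbox adds emails from an assigned supporter and allows up to eight calls in total on request.

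Table 1 ticks the row beginning "Clinical measures (from notes review" at 12 months for usual care, intervention, and intervention plus support. Separate rows for mortality and for the health economic data from notes review are ticked for the same three arms. The SAE section does not name the notes review as a source.

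**The concern.** Practices and facilitators have the same duty, but it begins only when they become aware of an event. Facilitator contact creates occasions for awareness in the support arm that are not described for the other two. No SAE enquiry common to all arms is described. Follow-up reminders reach everyone, but their stated purpose is to obtain the outcome measures. Adjudication cannot recover an event that nobody reported.

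If SAE counts are set out by arm, part of any excess in the support arm could reflect better detection rather than more events, while events in the web-only and usual-care arms could be under-counted. SAEs are the only adverse-event data collected. The stated aim is to test procedures intended for a main trial of over 20,000 patients. A difference in capture does not shrink as the sample grows, whereas the chance variation that would mask it does.

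**Working it through.** The document states no SAE rate, count or capture probability, so there is no figure of its own to reproduce. The arm sizes are consistent: 2 subgroups × 3 arms × 60 = 360, or 2 × 60 = 120 per arm with the subgroups pooled. The rest is illustration.

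**Inputs from the document**
- n = 120 per arm, pooled (Study Design).
- Scheduled contacts end at week 10 of a 12-month follow-up (Participant Timeline), so the share of follow-up covered is w = 10/52 = 0.192.
- Further contact on request is possible (TIDieR textbox). The extreme case is w = 1.

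**Assumed inputs**
- r: true proportion with an SAE over 12 months, the same in every arm and spread evenly over time.
- p: share of SAEs captured through participants and practices, the same in every arm (0.3 to 0.8 shown).
- q: share of otherwise missed SAEs that facilitators capture while in contact (0.25 to 0.5 shown; 0 means they add nothing).

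**Formulas**
- Expected count in another arm: n × r × p.
- Expected count in the support arm: n × r × [p + (1 − p) × q × w].
- Ratio: [p + (1 − p) × q × w] / p. It does not depend on r or n. It is 1 when q = 0 or p = 1 and cannot fall below 1.

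**Results for the ratio**

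| p | q | w | Support-arm capture | Ratio |
|---|---|---|---|---|
| 0.8 | 0.25 | 10/52 | 0.8 + 0.2 × 0.25 × 0.192 = 0.810 | 1.01 |
| 0.5 | 0.5 | 10/52 | 0.5 + 0.5 × 0.5 × 0.192 = 0.548 | 1.10 |
| 0.3 | 0.5 | 10/52 | 0.3 + 0.7 × 0.5 × 0.192 = 0.367 | 1.22 |
| 0.5 | 0.5 | 1 | 0.5 + 0.5 × 0.5 = 0.750 | 1.50 |
| 0.3 | 0.5 | 1 | 0.3 + 0.7 × 0.5 = 0.650 | 2.17 |

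**Ceiling for the scheduled contacts.** With p = 0.3 and perfect facilitator capture (q = 1) to week 10, capture is 0.30 + 0.70 × 10/52 = 0.435, and the ratio is 0.435/0.30 = 1.45.

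**In counts.** With r = 10%, p = 0.5 and q = 0.5, another arm expects 120 × 0.10 × 0.5 = 6.0 events. The support arm expects 6.6 (w = 10/52) or 9.0 (w = 1). From exact binomial distributions, the chance that the support-arm count exceeds that of one other arm is 0.51 or 0.75 respectively, against 0.44 with no difference in capture.

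**The case against.** The case for leaving the plan alone has several strands.

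- Practices are not merely invited to report. They have the same 24-hour duty, procedure and form as facilitators, for participants in every arm. This stands, and it limits the gap: the better practices report, the closer the ratio is to 1.
- Facilitator reporting is only described as possible, and the scheduled contacts are three brief ones ending at week 10. This also stands. A reader might infer that support-arm counts will certainly be higher, or will be two to three times those elsewhere. The scheduled contacts do not support that, since their ceiling at 30% base capture is about 1.45.
- A reader might infer that the steering committee will judge SAEs by arm. The text says only that SAEs are sent for adjudication. The analysis is descriptive, no between-arm SAE comparison is stated, and the stop or go criteria rest on data completeness, with recruitment feasibility and resources also considered. No decision rule in this trial depends on SAE counts by arm.
- Deaths are already collected equally through the mortality row of Table 1. This stands and narrows what has to be added. The fields of the notes review are not itemized, so whether admissions are already extracted cannot be told.
- The article condenses a fuller protocol, and the SAE procedure and form are not shown. Missing tabulation detail is therefore not the point. The point is the set of reporting sources that the article does state, which differs by arm.
- A facilitator who learns of an SAE must be able to report it, so some asymmetry comes with a supported arm. That is true, and it is a reason to keep this route for oversight but not to rely on it for counts by arm.

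Table 1 also ticks supporter use and supporter emails for both intervention arms, which does not fit the sections that place facilitator contact in the support arm. These need to be reconciled. Even on the Table 1 reading, usual care would still lack the facilitator route.

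**Conclusion.** The point holds in a limited form. As described, SAE ascertainment differs by arm: the support arm has one additional possible reporter with a duty to report, and the record review common to all randomized arms is not named as an SAE source. At equal true risk, the expected distortion in the support arm's count is zero or upward. A higher count in this trial is possible but not certain.

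The size rests entirely on assumed rates. The ratio is about 1.0 to 1.2 if facilitators capture up to half of otherwise missed events to week 10, with base capture of 30% to 80%. With 30% base capture, about 1.45 is the most that perfect capture in that window can give. About 2 requires year-long capture of half the missed events at 30% base capture. The practical consequence is confined to any descriptive SAE counts by arm and to adoption of the same procedure in the main trial.

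**What to change.** Keep expedited reporting from all present sources for safety oversight. For any SAE summary by arm, use a source common to the three randomized arms: the mortality data already collected, plus hospital admissions that meet the protocol's SAE definition (with its exclusions for pre-existing conditions and planned procedures), extracted at the 12-month notes review. Record the reporting source of each SAE and show facilitator-only reports separately, so that they are not compared across arms. State that this common source covers deaths and admissions, and not every SAE category.

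The cost is a few extraction fields and a little extra time on a review already planned for all randomized participants. No new contact with participants is needed. Since the article reports data collection as closed by May 2020, in this trial the change may amount to tabulating SAEs by source and using admissions where the notes review already recorded them. The full change can be written into the main trial's procedures.
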